## Abstract

**Background:** Crowding in the emergency department (ED) is a well-known problem resulting in an increased risk of adverse outcomes. Effective triage might counteract this problem by identifying the sickest patients and ensuring early treatment. In the last two decades, systematic triage has become the standard in ED's worldwide. However, triage models are also time consuming, supported by limited evidence and could potentially be of more harm than benefit. The aim of this study is to develop a quicker triage model using data from a large cohort of unselected ED patients and evaluate if this new model is non-inferior to an existing triage model in a prospective randomized trial.

**Methods:** The Copenhagen Triage Algorithm (CTA) study is a prospective two-center, cluster-randomized, cross-over, non-inferiority trial comparing CTA to the Danish Emergency Process Triage (DEPT). We include patients  $\geq 16$  years ( $n = 50,000$ ) admitted to the ED in two large acute hospitals. Centers are randomly assigned to perform either CTA or DEPT triage first and then use the other triage model in the last time period. The CTA stratifies patients into 5 acuity levels in two steps. First, a scoring chart based on vital values is used to classify patients in an immediate category. Second, a clinical assessment by the ED nurse can alter the result suggested by the score up to two categories up or one down. The primary end-point is 30-day mortality and secondary end-points are length of stay, time to treatment, admission to intensive care unit, and readmission within 30 days.

**Discussion:** If proven non-inferior to standard DEPT triage, CTA will be a faster and simpler triage model that is still able to detect the critically ill. Simplifying triage will lessen the burden for the ED staff and possibly allow faster treatment.

**Trial registration:** Clinicaltrials.gov: NCT02698319, registered 24. of February 2016, retrospectively registered

**Keywords:** Triage, Emergency Department, Vital signs

## Background

Crowding in emergency departments (ED) poses a serious patient safety concern in hospitals worldwide [1]. Since not every patient can be seen by a doctor on arrival, ED's prioritize patients according to their perceived urgency of care. In most hospitals today, this prioritization is done by systematic triage [2]. Patients are classified on the basis of a pre-specified algorithm into 5 acuity groups according to vital signs and primary symptom. Before systematic triage was introduced, a simple clinical assessment was used

to prioritize the succession in which patients were seen by doctors [2].

The first systematic triage model was introduced in a local hospital in Australia in the 1970s, and since then 4 triage models have become widespread: Australasian Triage Scale (ATS), Canadian Triage and Acuity Scale (CTAS), Manchester Triage System (MTS), and Emergency Severity Index (ESI) [2–5]. An overview of existing models is provided in Table 1. These models are widely used in their countries of origin, but they have also been implemented to varying degrees across the world, where local adaptations has been done [6–9]. In Scandinavia, Sweden was the first to focus on triage developing two different models: The Medical Emergency Triage and Treatment System and Adaptive Process Triage (ADAPT) [10].

\* Correspondence: [contact]

Department of Cardiology, Herlev-Gentofte Hospital, Copenhagen, Denmark  
Full list of author information is available at the end of the article

**Table 1** An overview of existing triage models

|                                               | DEPT                        | ATS                        | MTS                           | ESI                              | CTAS                          |
|-----------------------------------------------|-----------------------------|----------------------------|-------------------------------|----------------------------------|-------------------------------|
| Introduction                                  | 2009                        | 1994                       | 1996                          | 1999                             | 1995                          |
| Levels of triage                              | 5                           | 5                          | 5                             | 5                                | 5                             |
| Time to contact with doctor                   | 0 - 15 - 60 - 180 - 240 min | 0 - 10 - 30 - 60 - 120 min | 0 - 10 - 60 - 120 - 240 min   | 0 min - NS                       | 0 - 15 - 30 - 60 - 120 min    |
| Vital signs                                   | SAT, HR, BP, GCS, TP, RR    | BP, GCS, RR, HR, SAT, BSL  | Varies                        | HR, SAT, RR - TP a    | Varies                        |
| List of primary complaint                     | Yes                         | Yes                        | Yes                           | No                               | Yes                           |
| Other factors                                 |                             |                            |                               | Resources needed                 |                               |
| Inter-observer variability (Kappa/percentage) |                             | 38,7–79 %                  | K 0,48                        | K 0,78 b              | K 0,2–0,84                    |
| Mortality c                        | 11 - 2,2 - 1,2 - 0,5 % - NS | 12 - 2 - 1 - 0,3 - 0,03 %  | 10 - 0,04 - 0004 - 0002 - 0 % | 25 - 4 - 2 - 1 - 0 %             | 22 - 0,22 - 0031 - 0018 - 0 % |
| LOS                                           |                             |                            |                               | 4,7 - 4,3 - 4,3 - 7,3 - 2,0 days |                               |

DEPT Danish Emergency Process Triage, ATS Australasian Triage Scale, MTS Manchester Triage Scale, ESI Emergency Severity Index, CTAS Canadian Triage and Acuity Scale, SAT Blood Oxygen Saturation, HR Heart Rate, BP Blood Pressure, GCS Glasgow Coma Scale, TP Temperature, RR Respiratory Rate, BSL Blood Sugar Level, NS Not specified, LOS length of stay

aOnly measured for patients under < 3 years of age

bWeighted Kappa

cMortality measures were for different time intervals DEPT - In hospital, ATS - 24-h, MTS - In ED, ESI - 60 day, CTAS - In ED

ADAPT is rather similar to CTAS and ATS and it focuses on vital signs and the patient's presenting complaint.

In Denmark triage has been broadly implemented over the last decade [11]. Most ED's use a slightly modified version of ADAPT called Danish Emergency Process Triage (DEPT) [11–14].

Most triage models have been developed on the basis of expert opinion and they are not based on data from large prospective cohorts [15]. The models have then been implemented and retrospectively validated [5, 16–18]. The validation has focused on the respective models' inter-observer variability [15, 19] and ability to predict length of stay [20] and mortality [19, 21–23] but there are no prospective studies addressing if the models can prevent serious adverse events. Systematic triage takes time and prospective studies are needed to determine the future of ED triage [18].

Recently, data from ED visits have been collected over a period of 3 months at North Zealand Hospital giving a complete cohort of 6 000 patient ED visits [24]. This study confirmed earlier studies' conclusion that vital signs at admission are strong predictors of acute patient outcomes [21], and further demonstrated that a quick clinical assessment of patients by phlebotomists and medical students was superior in predicting 30-day mortality than formalized DEPT triage [25]. Based on these findings, our hypothesis was that a simple model of vital signs could be constructed that would perform as well as DEPT when combined with a quick clinical assessment by the ED nurse.

The aim of this article is to describe the design of the CTA, how the algorithm was designed and how it will be tested in a randomized controlled trial.

## Design

The study is a prospective two-center, cluster-randomized, cross-over, non-inferiority trial. CTA is compared to the preexisting DEPT. The primary aim of the CTA is to assess if it improves patient outcome, secondarily to obtain a faster ED acuity stratification. The primary end-point is 30-day mortality and secondary end-points are length of stay (LOS), time to treatment, admission to intensive care unit (ICU), and readmission within 30 days. Follow-up information will be attained from central registries.

## Setting and interventions

Two equally sized ED's in the capital region of Copenhagen are recruited to perform the study; Herlev Hospital and Bispebjerg Hospital with 70.000 and 85.000 annual admissions, respectively [26, 27]. Both centers are 24-h acute care hospitals offering broad medical, surgical, neurological, level-2 trauma and ICU services. The centers are randomly assigned to perform either CTA or DEPT triage as primary evaluation of patients. Subsequently, both hospitals will cross-over to use the other model. The number of admissions with CTA and DEPT will be 1:1. The CTA will be implemented during 2 weeks before initiation of data collection.

## Patient participation

In the study period, all patients admitted at any of the two centers will be included. Admission was defined as referral to a bed in the ED. The study design allows inclusion rate and adherence to the intervention to be close to 100 % as the two triage models will not be used at the same time and all acutely admitted patients are

categorized using triage. However, patients  $\leq 16$  years gynecology and obstetric patients will not be included since they are admitted directly to the respective department. Patients where major trauma is suspected pre-hospital will be admitted to a tertiary center in the region.

### Copenhagen Triage Algorithm

The CTA is based on vital signs and a clinical assessment by ED nurses.

The CTA classifies patients as red (resuscitation), orange (emergent), yellow (urgent), green (non-urgent) or blue (minor injuries and complaint) and this is done in two steps. A scoring chart based on vital signs is used to classify patients in an immediate category but a clinical assessment can alter the assigned category suggested by the score up to two classed up or one class down. The model is illustrated in Fig. 1. DEPT has a similar structure, but the classification depends on a more complex algorithm designed to classify patients based on their primary complaint (symptom) as well as vital signs [14]. DEPT only allows the ED nurses to reclassify patients as more urgent, not less. There will be no reclassification for the blue triage category as it is defined in the same way using CTA and DEPT for patients with minor injuries or complaints.

The cut-off points for vital signs (Fig. 1) of CTA were calculated using the results of the TRIAGE database [24]. This was done by defining either the 10 % highest (e.g. heart rate) or the 10 % lowest (e.g. systolic blood pressure) as abnormal, and using univariate logistic regression to determine its ability to predict 30-day mortality. The significant factors were then combined in a multivariate logistic regression with backwards elimination to determine the independent variables and their odds ratio in predicting 30-day mortality. These odds ratios were rounded to their nearest integer and combined to form a score.

The significant factors were systolic blood pressure < 100 mmHg, heart rate > 110 bpm, respiratory rate > 22 min, arterial oxygen saturation < 94 %, and treatment with oxygen (Fig. 1). Final categories were defined so that green patients had a 30-day mortality below

2.5 %, yellow patients had a 30-day mortality between 2.5 and 7.5 %, orange patients had a 30-day mortality between 7.5 and 15 % and red patients had a 30-day mortality above 15 %.

Results of the primary regression analyses using these cutoffs are shown in Table 2. Receiver-operating characteristics (ROC) curves showed that CTA and a quick clinical assessment performed by phlebotomists and medical students were superior to DEPT in identifying death within 30 days (Fig. 2). Area under the curve (AUC) statistics for the two models are presented in Table 3, which show that the CTA score is significantly superior to DEPT in predicting the risk of 30-day mortality.

### Sample size

The trial is designed as a non-inferiority trial, i.e. to show that 30-day mortality using CTA is not higher than using DEPT. The 30-day mortality in all admitted patients in the TRIAGE database was 4.2 % [24] and the 28-day mortality in the Acute Admission Database was 4.2 % [28]. Hence, we estimated the 30-day mortality to be 4.2 % for this study. Due to the estimated low incidence of the primary end-point, the proportional difference between the CTA and DEPT group (non-inferiority margin ( $\Delta$ )) is set at 0.5 %. The power to confirm non-inferiority is set at 80 % with a two-sided confidence interval of 95 %, which would require a sample size of 39,820. We chose to include a minimum of 40,000 patients. The combined percentage of admission to intensive or semi-intensive care unit in the TRIAGE database was 3.4 % [24], i.e. sample size should be adequate to prove non-inferiority for this secondary end-point as well. Reported 30-day readmission rate is usually around 10 % [29] meaning sample size will likely be sufficient to prove non-inferiority. In calculating the primary end-point of 30-day mortality, patients readmitted more than 30 days after discharge will be considered as separate encounters.

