### Statistics

Non-inferiority will be considered to have been confirmed if the lower bound of the 95 % two-sided confidence interval for the difference between the occurrence

| Factor                                                                                                                     |                         | Points | Red             | Orange           | Yellow               | Green         |
|----------------------------------------------------------------------------------------------------------------------------|-------------------------|--------|-----------------|------------------|----------------------|---------------|
| Oxygen treatment                                                                                                           | +                       | 4      | 8-14 points     | 4-7 points       | 2-3 points           | 0 points      |
| Systolic blood pressure                                                                                                    | < 100 mmHg              | 3      | Resuscitation   | Emergent         | Urgent               | Non-urgent    |
| Respiratory rate                                                                                                           | > 22 min   | 3      | Life threatened | Critical illness | Potentially unstable | Stable        |
| Heart rate                                                                                                                 | > 110 min  | 2      | Constant        | Re-evaluation    | Re-evaluation        | Re-evaluation |
| SpO 2                                                                                                           | < 94 %                  | 2      | Re-evaluation   | Every 15 min     | Every 60 min         | Every 180 min |
| A clinical assessment on arrival:                                                                                          |                         |        |                 |                  |                      |               |
| Triage nurse can move the patient one triage level down or up to two levels up based on his/her own evaluation of symptoms |                         |        |                 |                  |                      |               |

Red

Orange

Yellow

Green

**Fig. 1** The Copenhagen Triage Algorithm

**Fig. 1** The Copenhagen Triage Algorithm

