### Timeline

After a 1 week learning period for the staff, the study was initiated the 1st of March, 2015. Herlev Hospital was selected to begin with CTA, i.e. Bispebjerg Hospital continued their use of DEPT triage. This continued until the 17th of August 2015. Subsequently, the hospitals crossed-over. By the end of January 2016 the inclusion

**Table 3** Area under the curve results for the Receiver-Operating Characteristics for DEPT, CTA and a quick clinical assessment in the TRIAGE database

|                     | AUC  | Standard error |
|---------------------|------|----------------|
| CTA                 | 0735 | 0,02           |
| Clinical assessment | 0705 | 0,02           |
| DEPT                | 0605 | 0,02           |

stopped as planned. A total of approximately 50,000 patient visits have been recorded.

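### The stated inputs (4.2 % mortality, 0.5-point margin, 80 % power, two-sided 95 % CI) need about 50,530 patients, not 39,820; power at the planned minimum of 40,000 is about 70 %

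*Protocol*

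**What the plan says.** The Sample size section of the protocol takes one mortality figure for the whole trial: "Hence, we estimated the 30-day mortality to be 4.2 % for this study". It sets the margin at 0.5 %. It then states "The power to confirm non-inferiority is set at 80" %, "with a two-sided confidence interval of 95 %, which would require a sample size of 39,820", and concludes: "We chose to include a minimum of 40,000 patients".

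The Statistics section decides non-inferiority on the "lower bound of the 95 % two-sided confidence interval for the difference between the occurrence" of the primary endpoint in the two cohorts. The level used for sizing is therefore stated to be the level used for the decision. The protocol nowhere mentions a one-sided 5 % level or a 90 % interval for non-inferiority.

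Under Setting and interventions, allocation is balanced: "The number of admissions with CTA and DEPT will be 1:1". The abstract gives n = 50,000, and the Timeline, written after inclusion had closed, reports: "A total of approximately 50,000 patient visits have been recorded".

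**The concern.** For a non-inferiority comparison, one bound of a two-sided 95 % interval is a one-sided 2.5 % test, so the critical value is 1.960. The figure of 39,820 is too small for that value with the other inputs as stated. This calculation is the only quantitative justification of the trial's size, and the endpoint is mortality. If it is wrong, the protocol overstates the chance of confirming non-inferiority when the two triage models are truly equivalent. At the planned minimum, the risk of failing to confirm it would be about 30 % instead of the intended 20 %.

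**Working it through.** **Inputs from the protocol**
- Mortality 4.2 %, margin 0.5 %, power 80 %, two-sided 95 % CI (Sample size)
- Allocation 1:1 (Setting and interventions)

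**Assumptions that the protocol does not state**
- The true difference is zero, so mortality is 4.2 % in both arms.
- The margin is absolute, 0.005. This is the reading that reproduces the stated number.
- Patients are independent, with no allowance for clustering.

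**Formula**

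n per arm = (z_α + z_β)² × 2p(1 − p) / Δ²

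Here 2p(1 − p) / Δ² = 2 × 0.042 × 0.958 / 0.005² = 0.080472 / 0.000025 = 3,218.88.

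**Step 1: reproduce the stated figure**

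With z = 1.645 + 0.842: 2.487² × 3,218.88 = 6.18517 × 3,218.88 = 19,909.3, rounded up to 19,910 per arm. Total 2 × 19,910 = **39,820**, an exact match. Unrounded z-values give 19,901 per arm, or 39,802, within 0.05 %. The value 1.645 belongs to a one-sided 5 % test, equivalent to a two-sided 90 % CI.

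**Step 2: the level as stated**

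With z = 1.960 + 0.8416: 2.8016² × 3,218.88 = 7.84896 × 3,218.88 ≈ 25,265 per arm. Total **50,530**, and 50,530 / 39,820 = 1.27.

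**Step 3: other standard formulas at z = 1.96**

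| Method | Total N |
|---|---|
| Non-inferiority formula, continuity-corrected | 51,327 |
| Two-proportion formula, 4.2 % v 4.7 % | 53,396 |
| Two-proportion formula, 4.2 % v 3.7 % | 47,644 |

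The smallest of these is still about 20 % above 39,820 (47,644 / 39,820 = 1.20).

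**Step 4: power under the two-sided 95 % CI**

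Power = Φ(Δ / SE − 1.960), with SE = √(0.080472 / n per arm).

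| Total N | SE (percentage points) | Δ/SE − 1.960 | Power |
|---|---|---|---|
| 39,820 | 0.2010 | 0.527 | 70.1 % |
| 40,000 | 0.2006 | 0.533 | 70.3 % |
| 45,000 (illustration) | 0.1891 | 0.684 | about 75 % |
| 50,000 | 0.1794 | 0.827 | 79.6 % |

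With a one-sided 5 % level, power at 40,000 would be 80.2 %, which agrees with the protocol's claim.

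**Step 5: could an assumed benefit explain 39,820 at the stated level?**

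If CTA lowers mortality by d, n per arm = (z_α + z_β)² × [p(1 − p) + (p − d)(1 − p + d)] / (Δ + d)². At one-sided 2.5 %, d = 0.06 percentage points gives a total of 40,006 and d = 0.063 gives 39,567. A small assumed benefit would therefore bring the number close, but the protocol states none.

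**The case against.** Three points can be made for the protocol.

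*The one-sided level is an inference.* The protocol names no formula, software or assumed true difference, and a benefit of about 0.06 points at the stated level would also land near 39,800. A reader might infer that the authors certainly used a one-sided 5 % level; the text does not say so. What can be said is that this level reproduces the number to the last digit with the single mortality figure given, which makes it much the likelier explanation. The discrepancy does not depend on it: the inputs as written do not yield 39,820.

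*The trial did not stop at 40,000.* That number is a minimum, and about 50,000 visits were recorded, where nominal power is 79.6 %. A reader might infer that the trial as run had only 70 % power; the protocol does not support that. Nor does it assure 80 %. The Timeline counts visits, whereas the Sample size section treats a readmission as a separate encounter only if it comes more than 30 days after discharge. The analysable number may therefore be lower, and it is not given.

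*The decision rule is untouched.* The margin, the interval and the type I error stay as stated. A reader might also suspect that the mismatch prepares a later move to a 90 % interval. Nothing in the protocol points that way, since both sections fix 95 % two-sided.

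**Conclusion.** The stated sample size is wrong for the stated inputs, and no other part of the protocol repairs it. The requirement at the stated level is about 50,530, 27 % above 39,820, and power at the planned minimum is about 10 percentage points below the 80 % claimed. The error lies in the sizing statement, not in the analysis rule, and the number of visits recorded largely offsets it if most of them are analysable.

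The figures rest on a zero true difference, an absolute margin, 1:1 allocation and independent patients. The Limitations section accepts that clustering introduces dependence and that there are very few clusters. The powers above contain no allowance for this, and any residual cluster or period effect would lower them.

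**What to change.** - Keep the two-sided 95 % CI for the non-inferiority decision.
- In a dated correction, either replace 39,820 with about 50,530 (25,265 per arm), or keep the minimum of 40,000 and restate its power as about 70 %.
- Report the power at the number of analysable encounters actually reached, after the readmission rule is applied: about 80 % if that is 50,000, about 75 % if it were 45,000.
- Label every figure as assuming a zero true difference and making no allowance for clustering.
- Leave 40,000 on record as the planned minimum. Inclusion has closed, so presenting 50,000 as the planned size now would rewrite the plan after the fact.

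The cost is a change of text and one count from the existing data. No patients, procedures or analyses change.

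### The protocol says its sample size will likely suffice for non-inferiority on 30-day readmission but gives no readmission margin; with the only margin stated (0.5 points), power is about 38 % at 40,000 and 46 % at 50,000

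*Protocol*

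**What the plan says.** Readmission within 30 days is a listed secondary end-point (protocol, Abstract and Design). The Sample size section fixes the planning values for the primary end-point:

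- Event rate: "Hence, we estimated the 30-day mortality to be 4.2 % for this study".
- Margin: "the proportional difference between the CTA and DEPT group (non-inferiority margin ( $\Delta$ )) is set at 0.5" per cent. The reason given is that the primary end-point is expected to be rare.
- Error rates: "The power to confirm non-inferiority is set at 80 % with a two-sided confidence interval of 95" per cent.
- Size: "which would require a sample size of 39,820", followed by "We chose to include a minimum of 40,000 patients".

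The section then turns to two secondary end-points. On admission to intensive or semi-intensive care, at 3.4 %, it concludes that "sample size should be adequate to prove non-inferiority for this secondary end-point as well". On readmission it says: "Reported 30-day readmission rate is usually around 10 % [29] meaning sample size will likely be sufficient to prove non-inferiority". No margin or calculation accompanies the readmission sentence.

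The Statistics section keeps the same confidence level for the decision: "Non-inferiority will be considered to have been confirmed if the lower bound of the 95 % two-sided confidence interval". That rule is written for the primary end-point only. The Timeline section reports that inclusion has stopped, with about 50,000 visits recorded.

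**The concern.** The readmission sentence moves from a rate of about 10 % straight to a conclusion about sufficiency. For a fixed absolute margin the dependence runs the other way. The variance p(1 − p) increases with p up to 50 %, so a sample sized for a 4.2 % event is too small for a 10 % event at the same margin and power.

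Two misreadings could follow. A reader may believe that the trial can rule out a small increase in readmissions when, at the stated margin, it probably cannot. And if the readmission interval crosses a 0.5-point limit, that may be read as evidence against CTA, although such a result would be quite likely even if the two triage models performed identically.

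**Working it through.** **Inputs from the protocol.** Readmission rate 10 %, mortality rate 4.2 %, intensive or semi-intensive care admission 3.4 %, margin 0.5 points, two-sided 95 % interval, power 80 %, and minimum total 40,000 (all Sample size); 1:1 allocation (Setting and interventions); about 50,000 visits recorded (Timeline).

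**Assumptions added here.** Equal true rates in the two groups, independent patients, and the 0.5-point margin applied to readmission as an absolute difference.

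**Step 1: reproduce the protocol's own figure.** With n per group = (z_α + z_β)² × 2p(1 − p) / Δ², p = 0.042 and Δ = 0.005:

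- One-sided 5 %: (1.645 + 0.842)² × 0.08047 / 0.000025 = 19,901 per group, or 39,802 in total. This matches the stated 39,820 closely.
- Two-sided 95 % interval (one-sided 2.5 %): (1.960 + 0.842)² × 0.08047 / 0.000025 = 25,265 per group, or 50,530 in total. This does not match.

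So 39,820 is consistent with an absolute margin of 0.5 points and a one-sided 5 % level. The mismatch with the stated interval is a separate matter. It is used here only to justify showing both levels below.

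**Step 2: variance.** At 4.2 %: 0.042 × 0.958 = 0.0402. At 10 %: 0.10 × 0.90 = 0.0900. The ratio is 2.2.

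**Step 3: power for readmission.** SE = √(2p(1 − p) / (N/2)) and power = Φ(Δ/SE − z).

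- N = 40,000: SE = √(0.18 / 20,000) = 0.300 points. Power = Φ(1.667 − 1.960) = 38.5 %. At one-sided 5 %: Φ(1.667 − 1.645) = 50.9 %.
- N = 50,000: SE = √(0.18 / 25,000) = 0.268 points. Power = Φ(1.863 − 1.960) = 46.2 %. At one-sided 5 %: Φ(1.863 − 1.645) = 58.7 %.

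**Step 4: interval width.** The 95 % half-width is 1.96 × 0.300 = 0.59 points at 40,000 and 1.96 × 0.268 = 0.53 points at 50,000. Both exceed 0.5, so at this margin the criterion could be met only if the observed readmission rate were lower with CTA.

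**Step 5: what 80 % power would take (95 % interval).**

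- At 0.5 points: 2 × (2.8016)² × 0.18 / 0.000025 = 113,024 patients in total. At one-sided 5 % the figure is 89,030.
- At the available size: Δ = 2.8016 × SE, which is 0.84 points at 40,000 and 0.75 points at 50,000.

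**Step 6: sensitivity to the 10 % figure.** The rate comes from a cited source, so a range is shown. For true rates from 8 % to 12 %, power with the 95 % interval falls from 45 % to 34 % at 40,000, and from 54 % to 41 % at 50,000.

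**The case against.** The best defence is that the protocol never assigns 0.5 points to readmission. It sets that margin for mortality and justifies it by the low mortality rate, a reason that does not carry over to an event at 10 %. The authors may have had a wider margin in mind. One scaled to the rate would be 0.5/4.2 × 10 % = 1.19 points, which gives about 98 % power at 40,000.

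This stands as a limit on the conclusion. A reader might infer that the sufficiency claim is simply false. The protocol does not support that without condition, because the result depends on a margin it leaves unstated.

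The defence does not rescue the sentence, however. No wider margin appears anywhere. The preceding sentence about intensive care also fits an absolute margin better. Scaled to 3.4 %, the margin would be 0.40 points, and power there would be Φ(0.405/0.181 − 1.960), about 61 % at 40,000. With the stated interval, neither convention supports both sentences.

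Three further points on the other side:

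- **Size and level.** 40,000 is a minimum. At 50,000 visits and one-sided 5 %, power is 59 %, so failure cannot be called the expected outcome under every reading. It is still well short of 80 %.
- **A true benefit of CTA.** Power at 40,000 would be about 71 % if the true rates were 9.75 % against 10 %, and 92 % at 9.5 % against 10 %. The protocol assumes no such benefit for readmission.
- **Intensive care.** A reader might extend the criticism to that sentence. It should not be extended: at 0.5 points, power is 79 % at 40,000 and 87 % at 50,000. If the end-point is intensive care alone, its rate cannot exceed the combined 3.4 %, so power could only be higher.

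**Conclusion.** The point holds in conditional form. The readmission claim has no margin or calculation behind it, and it fails at the only margin the protocol states: about 38 % power at 40,000 and 46 % at 50,000 with the stated interval, or 51 % and 59 % at the looser level behind 39,820. No standard variant of the calculation at 0.5 points with equal true rates comes near 80 %.

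These figures treat patients as independent. The trial has two centres in a cluster cross-over, and the Limitations section acknowledges dependence and a very small number of clusters. Any net loss from clustering would lower power further, so the figures are best read as upper values in that respect.

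The consequence is moderate. Readmission is a secondary end-point, the sentence is hedged, it did not determine the sample size, and the primary conclusion does not rest on it. It still tells readers that the trial can probably do something that its stated inputs do not show.

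**What to change.** Take one of two routes.

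1. Delete the sufficiency claim for readmission. Report the difference in readmission rates with its 95 % confidence interval and draw no non-inferiority conclusion from it.
2. Before outcomes are analysed, state a readmission margin, justify it on clinical grounds rather than by the power it yields, and give the resulting power.

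If power at 0.5 points is quoted under either route, label it as an upper figure that ignores any net loss from clustering. The intensive care sentence needs no power restatement on this account.

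The cost is about two sentences and a less favourable statement about one secondary end-point. Inclusion has already stopped, so enlarging the sample is not an available remedy; the correction lies in the claim and in how the result is reported.
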